## 5. CLINICAL INVESTIGATION PROCEDURES

### 5.1 Study Participation Status

#### Provisionally enrolled:

Subjects who are fully informed about the specifics of the study by authorized site personnel and provide informed consent by properly signing an informed consent form after confirmation of the initial enrolment criteria are considered as provisionally enrolled. All provisionally enrolled subjects will receive a unique study participation number.

Subjects for whom consent was not obtained prior to participation in the study will not be considered provisionally enrolled. No data collected from these “subjects” will be included in any analysis.

#### Screen failure:

Provisionally enrolled subjects who withdraw consent prior to the index procedure or are unsuitable for treatment with the study device following e.g. laboratory assessments, pre-procedure ECG or any study specific invasive or non-invasive treatment as pre-specified in the clinical investigation, plan are considered as screen failure. These subjects will be exited from the study once screen failure is confirmed. Enrolment data and information regarding inclusion and exclusion criteria will be entered into the EDC for screen failures subjects and their informed consent forms will be kept in the site’s administrative files.

#### Enrolled:

Provisionally enrolled subjects who met all eligibility criteria are considered enrolled. Enrolled subjects will be followed in accordance with the clinical investigation plan.

#### Study exit:

Early termination of study participation applicable to subjects who have signed an informed consent form. It can be due to:

- Subject death
- Subject lost to follow up

- Subject withdrawal of informed consent
- Subject is considered as a screen failure
- Non-implanted subject, after the 1 month follow-up

Study completion: Subject who completes all protocol-required study procedures and follow ups.

## 5.2 Enrollment and Procedures

The enrollment and follow up process is outlined in the Figure 1 below.

[figure not shown]

### 5.3 Pre-screening

Subjects being considered for percutaneous coronary interventions should be pre-screened via a general review of inclusion/exclusion criteria without any study assessment. After the subject signed the approved informed consent, study specific screening assessments can be started.

### 5.4 Informed Consent Process

Informed consent should be obtained in accordance with the applicable regulations and current versions of Declaration of Helsinki, ICH-GCP and ISO 14155. Information to a potential subject shall be given in a prior interview in a layperson vocabulary and in the country's main language(s) with a member of the investigating team who is appropriately qualified under national law.

Informed consent shall be written, dated (including time of consent) and signed by the person performing the interview and by the subject himself or herself. During the consent process, the background of the proposed study, the benefits and risks and inconveniences of study participation should be explained in detail to the subject. Furthermore the conditions under which the clinical investigation is to be conducted, including the expected duration of the subject's participation, have to be elucidated.

It has to be emphasized that a subject's participation in the trial is voluntary and that the subject may refuse to participate or withdraw from the trial, at any time, without penalty or loss of benefits to which the subject is otherwise entitled. The possible alternative treatments, including follow-up measures if the participation of the subject is discontinued have to be explained. More details about the content of the patient information are kept in the Informed Consent Form.

The subject must be given ample time to read the subject information and to address questions before signing the consent form. The subject information and a copy of the EC approved signed consent form (by investigator and subject) will be handed out to the subject.

Subjects are considered *provisionally enrolled* in the study once they signed the informed consent signature form. A unique study identification number is then assigned to them by the EDC system. Provisionally enrolled subjects who do not fulfill the angiographic in- and exclusion criteria or who withdraw informed consent prior to the

study procedure are screening failure and need to be documented in the EDC (inclusion and exclusion criteria page, termination page).

## 5.5 Enrollment

Provisionally enrolled subjects are considered *enrolled* in the clinical investigation only after fulfilling the angiographic in- and exclusion criteria, assessed by diagnostic angiography before the index procedure.

The Intention to Treat (ITT) and the Per Protocol (PP) population will only be based on enrolled subjects.

All target lesions must be treated in one procedure. Planned staged procedures are not allowed within the BIOMAG-I study.

Only DREAMS 3G may be implanted during the index procedure unless a different treatment is required in case of an emergency situation.

If there is an attempt to implant the DREAMS 3G and the study device enters the guiding catheter, but the implantation is unsuccessful (e.g: target lesion not crossed) and a non-study device is implanted, the subjects will be followed up to 1 month.

Those subjects will only be considered for baseline characteristics analysis and device and procedure success evaluation and will be excluded from all angiographic and clinical endpoint analysis.

There is no restriction in the enrolment of subjects per site and enrolment will end once up to 115 subjects have been included in the study.

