### 7.1 Study Populations

Primary and secondary endpoint analysis will be conducted on the following pre-defined analysis populations:

- Intent-to-treat population (primary analysis)
  - Subjects for whom an investigational scaffold enters the guide catheter following the diagnostic angiography, regardless of whether the investigational scaffold is implanted in the intended location or not.
  - Subjects who received an investigational scaffold and who are later determined not to meet study eligibility criteria or who have CIP violations.

*Note:* Subjects, for whom DREAMS 3G entered the guiding catheter following the diagnostic angiography but who are not implanted (e.g. a different device had to be implanted) will be followed up until 1 month. Only baseline characteristics, device and procedure success, and safety up to 1 month will be reported for them.

- Per protocol population
  - Subjects implanted with the investigational scaffold at the intended location and who do not deviate from any relevant eligibility criteria and complete the study follow-up requirements without any relevant CIP violation.

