### **INTENT-TO-TREAT**

The intention-to-treat (ITT) population includes all subjects in whom scaffold implantation is attempted (i.e. the clinical investigation scaffold has entered the guiding

catheter). In case a different device needs to be implanted and the patient did not receive a DREAMS 3G scaffold, the patient will be excluded from all angiographic and clinical endpoint analysis. Those patients will be included for device and procedure success analysis only.

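### Sections 5.5, 7.1 and Appendix 2 give three incompatible rules for subjects with an attempted but not implanted scaffold, and two of the rules take them out of the 1-month event rates of the ITT population

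*Protocol*

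**What the plan says.** Section 7.1 makes the ITT population the primary one for primary and secondary endpoints. It admits every subject whose scaffold enters the guide catheter after the diagnostic angiogram, "regardless of whether the investigational scaffold is implanted in the intended location or not".

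Three places then say what happens to attempted subjects who end up without a DREAMS 3G:

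- **Section 5.5:** "Those subjects will only be considered for baseline characteristics analysis and device and procedure success evaluation". They "will be excluded from all angiographic and clinical endpoint analysis".
- **Section 7.1, note to the ITT definition:** "Only baseline characteristics, device and procedure success, and safety up to 1 month will be reported for them".
- **Appendix 2, Intent-to-treat:** "the patient will be excluded from all angiographic and clinical endpoint analysis", followed by "Those patients will be included for device and procedure success analysis only".

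Sections 5.1, 5.5, 5.13 and 7.1 agree that these subjects are followed to 1 month and then leave the study. Section 4.8 schedules target lesion failure (TLF), cardiac death, target-vessel MI, clinically driven target lesion and target vessel revascularisation (TLR, TVR) and scaffold thrombosis at 1 month, among other times. Section 7.3 estimates them by Kaplan-Meier.

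**The concern.** Each of the three statements limits what is done with these subjects, and the limits differ. A statistician cannot comply with all three, and an analysis plan written later would have to depart from at least one of them.

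The choice matters because a failed delivery or a switch to another device is an outcome of the attempted treatment. Removing subjects on that basis selects on a post-attempt device outcome. If their early event risk is higher than that of implanted subjects, which is plausible but not quantified in the protocol, the reported 1-month rates come out too low. The label would still say ITT, in a first-in-man study whose stated objective includes safety and which supports CE approval. The relevant month of follow-up is collected in any case.

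**Working it through.** **1. The three rules side by side**

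| Place | Literal trigger | Kept for | Excluded from |
|---|---|---|---|
| Section 5.5 | Implantation fails and a non-study device is implanted | Baseline data, device and procedure success | All angiographic and clinical endpoints |
| Section 7.1 note | Scaffold entered the catheter, subject not implanted (another device is given as an example) | Baseline data, device and procedure success, safety to 1 month | Everything else, by implication |
| Appendix 2 | A different device is needed and no DREAMS 3G was received | Device and procedure success | All angiographic and clinical endpoints |

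The three kept sets are all different, and each is worded as exhaustive. Two of the three state the exclusion from clinical endpoints.

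**2. The triggers also differ.** Section 4.9 allows two target lesions. A subject with one implanted DREAMS 3G and one failed attempt treated with another stent meets the literal trigger of Section 5.5 but not that of Appendix 2. An attempted subject who receives no device at all is covered by Section 7.1 but not literally by the other two.

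**3. Possible number of such subjects.** The protocol gives no rate, so this is an assumption. Two figures serve as a guide:
- Section 1.1.3 reports 99% implant success for the predecessor in the post-market survey: 1% of 115 is about 1 subject.
- Table 3 gives 0-7% for scaffold system events, a category wider than failed delivery: 7% of 115 is about 8 subjects.

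**4. Effect on a 1-month event rate.** Exact (Clopper-Pearson) 95% limits are used. For 0 events the upper limit is 1 − 0.025^(1/n). For x events it is the 97.5th percentile of Beta(x + 1, n − x).

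| Assumed scenario (115 attempted) | Non-implanted excluded | All attempted included |
|---|---|---|
| 2 not implanted, 1 event among them, none elsewhere | 0/113 = 0%, upper limit 1 − 0.025^(1/113) = 3.2% | 1/115 = 0.9%, upper limit 4.7% |
| 1 not implanted, with an event; 1 event among implanted | 1/114 = 0.9% (0.0 to 4.8%) | 2/115 = 1.7% (0.2 to 6.1%) |
| 8 not implanted, 1 event among them; 1 event among implanted | 1/107 = 0.9% (0.0 to 5.1%) | 2/115 = 1.7% (0.2 to 6.1%) |
| 8 not implanted, no event among them; 1 event among implanted | 1/107 = 0.93% | 1/115 = 0.87% |

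Where a non-implanted subject has an event, exclusion roughly halves the rate or makes it zero. Where none has, exclusion raises it very slightly. So the downward bias is possible, not certain.

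**5. Primary endpoint and sample size.** The plan's figures reproduce. For a one-sample t-test with one-sided alpha 0.025 and noncentrality 0.145·√n/SD:
- 6 months, SD 0.34: n = 74, power 95.2%; 74/0.85 = 87.1, so 88 enrolled.
- 12 months, SD 0.35: n = 78, power 95.1%; 78/0.75 = 104 enrolled.

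With 1 to 8 of 115 subjects not implanted and the stated dropout, 96 to 90 remain at 6 months (power 98.5% to 97.9%) and 85 to 80 at 12 months (power 96.5% to 95.5%). Both stay above the planned 95%.

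**The case against.** - **Failures are not invisible.** Device and procedure success are listed among the clinical secondary endpoints in Section 4.8, and all three rules keep non-implanted subjects in both. Procedure success already fails on in-hospital death, MI or repeat target lesion revascularisation. This stands, so it would be wrong to infer that failures leave every clinical endpoint. What is lost is their contribution to the separate event rates, including events between discharge and day 30.
- **Section 7.1 does not literally put them in the TLF rate.** It promises safety to 1 month, which could mean adverse events reported alongside the endpoints. This stands too: the 1/115 figure shows what including all attempted subjects would give, not what Section 7.1 unambiguously prescribes. Even so, the kept sets still conflict, and the ITT definition still admits subjects whom two other places take out.
- **Events are still collected and reviewed.** Section 6.1 requires all events to be reported for fully enrolled subjects, and Sections 8.1.1 and 8.1.2 provide for board review and adjudication. That protects oversight. It does not settle the reported rates.
- **Some endpoints have no meaning without a scaffold.** In-scaffold late lumen loss and scaffold thrombosis are examples, and leaving these subjects out of them is unavoidable. The fix is limited accordingly.

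Two stronger readings are tempting, and the text does not support them. Section 5.1 says "Provisionally enrolled subjects who met all eligibility criteria are considered enrolled", while Section 7.1 keeps implanted subjects later found ineligible. These agree if eligibility is taken as judged at enrolment, and Section 8.6.1 foresees violations of the criteria. A reader might also infer that these subjects' events could escape the stopping rules, but Section 9.7 counts recruited patients and does not restrict the tally to implanted ones.

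**Conclusion.** The contradiction is real and can be seen from the text alone. If Section 5.5 or Appendix 2 is followed, the 1-month rates of TLF, cardiac death, target-vessel MI and clinically driven TLR and TVR are as-treated rates presented as ITT, and they can be biased downward. The size rests on an assumed small number of non-implanted subjects and an assumed event among them. At the low counts expected at 1 month, one such event moves the upper confidence limit from 3.2% to 4.7% in the first illustration.

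Severity is moderate. The primary late lumen loss test and the sample size are untouched, the 1-month rates are descriptive with no hypothesis test, and few subjects are likely to be concerned. The rule should nevertheless be settled before the data are analysed, because it decides who enters the reported safety rates.

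**What to change.** Put one rule in Sections 5.5 and 7.1 and in Appendix 2:

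1. All subjects in whom the scaffold entered the guiding catheter count in device and procedure success and in the 1-month patient-level event endpoints (TLF, cardiac death, target-vessel MI, clinically driven TLR and TVR). The non-implanted are censored at their 1-month exit in the Kaplan-Meier analysis.
2. Late lumen loss, other imaging endpoints and scaffold thrombosis are analysed in a separately named implanted set.
3. The trigger is worded identically everywhere. It covers attempted subjects who receive no device, and says how a two-lesion subject with one implanted and one failed scaffold is classified.
4. One sentence says how TLR is read for a lesion without a DREAMS 3G. Appendix 2 counts an attempted lesion as a target lesion but sets the TLR region by the scaffold edges.

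The cost is an amendment of wording, including that one clarification. No new data are needed, since the 1-month follow-up is already planned. Event rates may look slightly less favourable.

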## 5.6 Baseline Examinations

The subjects' clinical investigation eligibility must be confirmed prior to the intervention through the following tests and examinations:

- Demographics
- Review of in- and exclusion criteria
- Physical examination and relevant medical history including angina status or myocardial ischemia
- Within 72 hours prior to study procedure:
  - For women of child-bearing potential < 55 years, a pregnancy test must be performed
  - Serum creatinine assessment
- Within 24 hours prior to study procedure:
  - Cardiac biomarkers CK, CK-MB and Troponin (assessment of CK-MB is mandatory)
  - A 12-lead electrocardiogram

## 5.7 Medication guidelines

Following medication regimen is recommended throughout the clinical investigation.

**Table 4: Overview medication guideline**

| Timing             | Medication                       | Procedure                                                                                                                                             |
|--------------------|----------------------------------|-------------------------------------------------------------------------------------------------------------------------------------------------------|
| Prior to Procedure | Heparin                          | Left to the discretion of the cardiologist                                                                                                            |
|                    | ASA                              | 75 mg for 3 days prior to procedure or a peri-procedural dose of 250-500mg at the discretion of the cardiologist.                                     |
|                    | Clopidogrel                      | Loading dose of 300- 600 mg < 6 hours prior or during the intervention
Subjects on Clopidogrel therapy (at least 7 days): no loading dose required |
| During Procedure   | IV LMWH / Unfractionated Heparin | Per routine hospital practice. It is recommended to maintain an ACT > 250 seconds                                                                     |
|                    | IIb/IIIa Inhibitor               | Left to the discretion of the cardiologist                                                                                                            |
|                    | Intracoronary Nitroglycerin or,  | 100-200 µg prior to baseline and post intervention angiograms                                                                                         |

| Timing                                                                                                                                                                                                                                                                                                                                                                                                                                                                                                                                                                                         | Medication                               | Procedure                                                             |
|------------------------------------------------------------------------------------------------------------------------------------------------------------------------------------------------------------------------------------------------------------------------------------------------------------------------------------------------------------------------------------------------------------------------------------------------------------------------------------------------------------------------------------------------------------------------------------------------|------------------------------------------|-----------------------------------------------------------------------|
|                                                                                                                                                                                                                                                                                                                                                                                                                                                                                                                                                                                                | Intracoronary
Isosorbide
Dinitrate | 1-3 mg prior to baseline and post intervention angiograms             |
| Post-Procedure                                                                                                                                                                                                                                                                                                                                                                                                                                                                                                                                                                                 | IIb/IIIa Inhibitor                       | Per routine hospital practice                                         |
|                                                                                                                                                                                                                                                                                                                                                                                                                                                                                                                                                                                                | ASA                                      | 75 to 320 mg per day                                                  |
|                                                                                                                                                                                                                                                                                                                                                                                                                                                                                                                                                                                                | Clopidogrel                  | 75 to 150 mg per day                                                  |
| Discharge                                                                                                                                                                                                                                                                                                                                                                                                                                                                                                                                                                                      | ASA                                      | 75 to 330 mg per day, lifelong                                        |
|                                                                                                                                                                                                                                                                                                                                                                                                                                                                                                                                                                                                | Clopidogrel                  | 75 to 150 mg per day for a minimum of 6 months unless contraindicated |
| 
Cardiologist may substitute to Prasugrel, Ticlopidine or Ticagrelor for subjects who are allergic, hypersensitive or resistant to Clopidogrel. Subjects on Ticlopidine must have CBC(s) performed per instructions for use.
 
Recommendation: If a subject requires OAC after DREAMS 3G implantation, DAPT should be maintained until 6 months follow up. Afterwards DAPT can be downsized to either ASA or Clopidogrel alone together with OAC for the remaining time period up to 12 months. After this, OAC monotherapy can be prescribed if still required.
 |                                          |                                                                       |

